**Porto Alegre, 2014**

1. **Abstract:**

*Background*: Liberation from mechanical ventilation is an essential component in caring critically ill patients with Chronic Obstructive Pulmonary Disease (COPD). *Objective*: To compare spontaneous breathing trials (SBT) performed with pressure-support (PS) with T-Piece for weaning patients with COPD from mechanical ventilation. *Design*: randomized controlled trial. *Methods*: Patients with clinical diagnosis of COPD, admitted to intesive care unit (ICU) and mechanically ventilated for more than 48 hours will be included. When considered able to test spontaneous breathing, according to institutional protocols, patients will be randomized for SBT through PS or T-piece. Primary outcome will be duration of mechanical ventilation. Other assessed outcomes will be ICU mortality, extubation success, weaning duration, ICU length of stay and tracheostomy incidence. *ClinicalTrials.gov* Register NCT01464567.

**2. Background:**

Chronic Obstructive Pulmonary Disease (COPD) is a prevalent nosologic entity, being among the most frequent ICU mortality causes worldwide. Among patients with COPD, acute respiratory failure is the main reason for ICU admission, warranting, commonly, invasive MV.

MV is an essential component of life support when respiratory failure presents. There are, however, inherent adverse consequences specific to the patients with COPD. Once these patients have dynamic flow obstruction, MV can result in air trapping, barotrauma, hemodynamic compromise and respiratory muscle fatigue. Likewise, as soon as the primary condition that resulted in respiratory failure is controlled, one must consider starting MV liberation.

Liberation from MV consists on gradual ventilatory support withdrawal until the patient is considered able to resume unassisted ventilation. Spontaneous Breathing Trials (SBT) are a fundamental step to assess actual conditions that patients have to proceed ventilatoy withdrawal. Specific parameteres to define precisely when to start SBTs are unavailable. If made too early, SBTs may result in respiratory fatigue; if too late, may coexist with muscle deconditioning, ventilator-associated pneumonia and increased ICU length of stay. It is estimated that MV liberation process can be responsible for over 40% of the total duration of MV; for patients with COPD, this interval could be even higher.

SBTs can be done through different techniques. One can use a T-piece connector attached to an enriched oxygen supply, while allowing spontaneous ventilation, disconnected from the ventilator. This method is associated with increased work of breathing through the increased airway resistance imposed by the internal diameter of the endotracheal tube, unassisted of positive pressure.

For counterbalancing this mechanism, one can use positive pressure to overcome this effect. SBTs using Pressure-Support (PS) are performed with positive inspiratoy pressures between 5 and 10cmH2O, theoretically sufficient to copensate the increase in the work of breathing.

Estaben et al compared 4 methods of performing SBTs in 130 patients (32% of whom with COPD), randomly allocated to Intermittent Mandatory Ventilation, PS, once-a-day T-piece or multiple T-piece during the day. T-piece SBTs allowed faster extubation and less MV duration. Brochard et al drawn a similar study, in which 109 patients were allocated to 3 different SBTs, including T-piece and PS. These authors reported lower extubation failure rates with PS than with T-piece. Both studies indicated that Intermittent Mandatory Ventilation results in less favorable outcomes. Other recent trials suggest that PS and T-piece have similar results.

Regarding specifically patients with COPD, a recent trial compared SBT strategies. Matic et al included 63 patients who had already a SBT failure and found a lower ICU length of stay using PS compared to T-Piece. Nevertheless, study design limitations and the non-standardization of non-invasive ventilation use limit the interpretation of these results.

Therefore, the best strategy to proceed MV liberation for patients with COPD is still unclear, warranting the performance of the present randomized controlled trial.

**3. Objectives:**

**3.1 Primary:**

To compare SBTs using PS with T-piece regarding MV duration, in patients with COPD mechanically ventilated for at least 48 hours.

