**3.1 Secondaries:**

To compare, between the aformentioned SBTs, the following outcomes:

- ICU length of stay;
- Time to liberation from MV (weaning duration);
- Extubation failure rates;
- Mortality;
- Tracheostomy incidence.

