**5.2.4 Data assessment and randomization:**

Patient inclusion will be made only after individuals complete 48 hours from MV initiation, and after informed consent obtainance. Data will be collected in prespecified charts, omitting patients’ identification.

As soon as the individual is considered able to perform a SBT, the randomization procedure is performed, defining study group: SBT through T-Piece or SBT through PS. Randomization will be in blocks of 10, according to the SAPS III (simplified acute physiology score, version 3) score. Randomization will be done using sealed numbered opaque envelopes.

Patients allocated to the PS group will have inspiratory pressure level reduced to 10cmH2O to attenuate airway resistance imposed by the mechanical apparatus. Patients allocated to the T-piece group will have their endotracheal tubes disconnected from the ventilator and attached to a T-connector, which permits connection to an oxygen-enriched supply while breathing at room air pressure.

Patients will be continuously monitored according to heart and respiratory rate, arterial pressure and pulse oximetry. SBTs will have 30-minutes duration in both groups.

Extubation will be performed according to predefined criteria, as previously published: respiratory rate > 35 breaths/min, oxygen saturation < 88%, heart rate > 140/min, systolic blood pressure > 200 mmHg or < 80 mmHg (or any variation exceeding 30% difference from the baseline), exaggerated use of accessory respiratory muscles, consciousness disturbance, diaphoresis or new arrhythmia. Patients who failed SBT were returned to their previous MV settings for at least 24 hours. The same SBT randomized modality was maintained for further SBTs.

Following extubation, all patients will be preemptively connected to non-invasive mechanical ventilation.

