**5.2.5 Statistical analysis:**

Data will be stored and analysed using the Software SPSS Statistics 18.0. Continuous variables will be presented as means and standard deviation or medians and interquartile intervals. Student’s t test or Wilcoxon-Mann-Whitney test will be used for comparisons. Categorical variables will be reported as percentages and compared by chi-square test or Fisher exact test, when appropriate.

Statistical significance level will be considered a two-tailed p-value lower than 0,05.

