**5.2.6 Sample size calculation:**

We used the mean MV duration for individuals with COPD admitted to the ICU of Hospital Nossa Senhora da Conceição of 5.8 (± 2.44) days to estimate sample size. Therefore, 95 patients in each group must be included to detect a 1-day reduction, considering a study power of 80%.

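### The primary outcome includes ventilator days accrued before randomisation, and the stated unadjusted test gives up precision that a baseline covariate could recover

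*Protocol*

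**What the plan says.** The Abstract says "Primary outcome will be duration of mechanical ventilation", and section 3.1 (Primary) sets the objective as "To compare SBTs using PS with T-piece regarding MV duration, in patients with COPD mechanically ventilated for at least 48 hours". Neither gives a start or stop for the clock. Three other places point to total ventilation time:

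- Section 3.1 (Secondaries) lists weaning duration as a separate, secondary outcome.
- Section 2 treats weaning as one part of the whole: "MV liberation process can be responsible for over 40% of the total duration of MV". It adds that the share could be higher in COPD.
- Section 5.2.6 bases the sample size on the "mean MV duration for individuals with COPD admitted to the ICU" of one hospital, 5.8 days with SD 2.44.

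On timing, section 5.2.4 says "Patient inclusion will be made only after individuals complete 48 hours from MV initiation", and then "As soon as the individual is considered able to perform a SBT, the randomization procedure is performed". Randomisation is in blocks of 10 according to SAPS III, not according to earlier ventilation time.

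On analysis, section 5.2.5 says for continuous variables that a "t test or Wilcoxon-Mann-Whitney test will be used for comparisons". It names no covariate.

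**The concern.** Days on the ventilator before randomisation are fixed and known when the envelope is opened. They are also an exact additive part of the primary outcome: total days = days before randomisation + days after. The SBT technique can act only on the second part.

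An unadjusted comparison of totals carries the patient-to-patient spread of the first part into the standard error. Any chance difference between the arms in earlier days passes day for day into the estimated effect. An analysis that uses the known baseline value can remove this noise without changing the outcome. At stake is the precision of the trial's main comparison at the planned 190 patients.

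**Working it through.** **Inputs from the protocol.** SD 2.44 days, mean 5.8 days, target difference 1 day, power 80%, 95 per group (section 5.2.6); two-sided 0.05 (section 5.2.5); weaning share over 40% (section 2).

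**Input not in the protocol.** R², the share of the variance of total MV duration explained by days before randomisation. It is assumed below, over a range that includes zero.

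**Step 1: reproduce the stated figure.** Normal approximation: n = 2 × (2.44 × (1.960 + 0.842) / 1)² = 93.5, so 94 per group. The t-based calculation gives 94.4, so 95 per group, as stated. Power at 95 per group is 80.2% (t-based).

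**Step 2: effect of adjustment.** Residual SD = 2.44 × √(1 − R²). Power is for a 1-day difference at 95 per group, two-sided 0.05, t-based. The detectable difference at 80% power scales with the residual SD.

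| Assumed R² | Residual SD (days) | Power at 95 per group | Detectable difference (days) |
|---|---|---|---|
| 0 | 2.44 | 80% | 1.0 |
| 0.10 | 2.31 | 84% | 0.95 |
| 0.20 | 2.18 | 88% | 0.89 |
| 0.30 | 2.04 | 92% | 0.83 |
| 0.50 | 1.73 | 98% | 0.70 |

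**Step 3: adjusting compared with restarting the clock.** Let a and b be the SDs of days before and after randomisation, and r their correlation, with a² + b² + 2rab = 2.44². Counting only from randomisation leaves SD b. ANCOVA leaves b × √(1 − r²), which is never larger.

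- a/b = 1, r = 0: both leave SD 1.73 and need 47 per group.
- a/b = 0.5, r = −0.6: b = 2.44 / √(0.25 + 1 − 0.6) = 3.03, and counting from randomisation needs 144 per group. ANCOVA leaves 2.42 and needs 93.
- a/b = 0.5, r = −0.5: the covariance of earlier days with the total is a² + rab = 0.25b² − 0.25b² = 0, so ANCOVA gains nothing.

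Over a grid of a/b from 0.5 to 1.5 and r from −0.6 to +0.6, ANCOVA needed 12 to 93 per group, against 94 unadjusted (normal approximation).

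**Step 4: the 1-day target in context.** As a share of total MV, 1 / 5.8 = 17%. If post-randomisation time is taken as the weaning share, a 40% share gives 0.40 × 5.8 = 2.32 days and 1 / 2.32 = 43%. An assumed 60% share gives 3.48 days and 1 / 3.48 = 29%.

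**The case against.** The strongest reply is that nothing here is wrong. The SD of 2.44 describes total MV duration, so the spread of earlier days is already inside the sample size, and the trial has the power it claims. Randomisation balances earlier days in expectation, and the test's standard error covers chance imbalance. Total MV duration is a defensible primary outcome, and weaning duration is reported anyway as a secondary. Covariates are often chosen in the SAP, and section 5.2.5 is one general sentence for all continuous variables.

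Most of this stands. A reader might infer that the result would be biased or that the trial is underpowered. The protocol's own figures support neither, as Step 1 shows. A reader might also take 43% as the estimate of how much weaning time must be saved. It is a ceiling, because section 2 says over 40% and possibly more in COPD. The 5.8-day mean is also not stated to come from patients ventilated for at least 48 hours. Nor can a large gain be presumed: the protocol gives no SD for earlier days, and Step 3 has a case with no gain.

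Two parts do not answer the point. A secondary outcome does not sharpen the comparison on which the trial is powered. And although a SAP could add a covariate, the protocol does not merely leave the method open: it names unadjusted two-group tests, and its sample size matches one.

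**Conclusion.** The point holds as an avoidable loss of precision and is worth acting on, though the trial is sound without it. It rests on reading the primary outcome as total MV time, which is the reading that fits sections 2, 3.1 and 5.2.6 together.

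The gain runs from nothing, if earlier days explain none of the variance, to about 98% power if they explain half. Even a 10% share would bring 80% up to about 84%. Which of these applies cannot be settled from the protocol.

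It may be tempting to conclude that the clock should start at randomisation. The protocol does not support that as the remedy: it would turn the primary outcome into something close to the existing secondary outcome, weaning duration. It could also lose precision if earlier and later days are strongly negatively correlated.

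**What to change.** In section 5.2.5, keep total MV duration as the primary outcome and state that it will be analysed with a linear model (ANCOVA) containing treatment arm and MV days before randomisation. The model estimates the same difference in total MV days. If the distribution is skewed, use a covariate-adjusted alternative, such as a rank-based ANCOVA, and leave the outcome's start time unchanged. It would also help readers if section 5.2.6 showed the 1-day target against the expected post-randomisation time, as a range.

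The cost is a sentence of text and slightly more analysis work. The start of ventilation is already needed for the 48-hour criterion, and the time of randomisation is known for every patient. Neither the number of patients nor any study procedure changes.

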**3.1 Secondaries:**

To compare, between the aformentioned SBTs, the following outcomes:

- ICU length of stay;
- Time to liberation from MV (weaning duration);
- Extubation failure rates;
- Mortality;
- Tracheostomy incidence.

**4. Equipoise:**

COPD is a commonly encountered comorbidity in patients with acute respiratory failure in ICUs worldwide, being associated with prolonged mechanical ventilation, increased length of stay and extubation failures.

Once extubation failure rates could be over 40% in this population, criterious assessment of which patients are suitable to MV liberation is warranted. This can be done by different ways, being SBTs with T-Piece and PS the most common approaches.

If SBTs through T-Piece seems to be more specific to detect extubation failures, this also can precipitate muscle fatigue and air trapping, specially in patients with dynamic airflow obstruction. In contrast, SBTs with PS intend to attenuate work of breathing and airway resistance, even if this does not reproduce actual post-extubation scenario.

Once this question is still unclear and the condition to be studied is highly prevalent, the performance of this trial is justified.

**5.2 Patients:**

**5.2.1 Inclusion criteria:**

Consecutive patients with COPD will be included if older than 18 years, admitted do the participant ICUs and mechanically ventilated for at least 48 hours.

Diagnosis of COPD will be made by clinical assessment, review of medical recordsand biochemical and radiologial data.

**5.2.2 Exclusion criteria:**

- Tracheostomy installation before the start of MV liberation procedure;

- Refuse to deliver informed consent;

- Individuals allocated in another clinical trial.

**5.2.3 Design:**

Randomized controlled trial.

This study was previously registerd at ClinicalTrials.gov under registration number NCT01464567.

**5.2.4 Data assessment and randomization:**

Patient inclusion will be made only after individuals complete 48 hours from MV initiation, and after informed consent obtainance. Data will be collected in prespecified charts, omitting patients’ identification.

As soon as the individual is considered able to perform a SBT, the randomization procedure is performed, defining study group: SBT through T-Piece or SBT through PS. Randomization will be in blocks of 10, according to the SAPS III (simplified acute physiology score, version 3) score. Randomization will be done using sealed numbered opaque envelopes.

Patients allocated to the PS group will have inspiratory pressure level reduced to 10cmH2O to attenuate airway resistance imposed by the mechanical apparatus. Patients allocated to the T-piece group will have their endotracheal tubes disconnected from the ventilator and attached to a T-connector, which permits connection to an oxygen-enriched supply while breathing at room air pressure.

Patients will be continuously monitored according to heart and respiratory rate, arterial pressure and pulse oximetry. SBTs will have 30-minutes duration in both groups.

Extubation will be performed according to predefined criteria, as previously published: respiratory rate > 35 breaths/min, oxygen saturation < 88%, heart rate > 140/min, systolic blood pressure > 200 mmHg or < 80 mmHg (or any variation exceeding 30% difference from the baseline), exaggerated use of accessory respiratory muscles, consciousness disturbance, diaphoresis or new arrhythmia. Patients who failed SBT were returned to their previous MV settings for at least 24 hours. The same SBT randomized modality was maintained for further SBTs.

Following extubation, all patients will be preemptively connected to non-invasive mechanical ventilation.

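### Several ICUs recruit, but the stated blocking and the stated test leave ICU out, while the planning SD comes from one hospital's ICU: a small loss of precision that is cheap to recover

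*Protocol*

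**What the plan says.** - **Setting.** Protocol 5.2.1 takes patients "admitted do the participant ICUs and mechanically ventilated for at least 48 hours", so more than one ICU takes part. The text at hand does not give the number.
- **Trigger for randomisation.** The Abstract states: "When considered able to test spontaneous breathing, according to institutional protocols, patients will be randomized for SBT through PS or T-piece". Section 5.2.4 adds no common readiness criteria.
- **Allocation.** Section 5.2.4 states: "Randomization will be in blocks of 10, according to the SAPS III (simplified acute physiology score, version 3) score", and then "Randomization will be done using sealed numbered opaque envelopes". ICU is not named as a factor. The section does not say whether there is one envelope series or one per ICU.
- **Outcome and test.** The Abstract states: "Primary outcome will be duration of mechanical ventilation". Section 5.2.5 states: "Student’s t test or Wilcoxon-Mann-Whitney test will be used for comparisons". No ICU term is mentioned. The threshold is two-sided: "Statistical significance level will be considered a two-tailed p-value lower than 0,05".
- **Sample size.** Section 5.2.6 uses the mean MV duration of COPD patients in one named hospital's ICU, "of 5.8 (± 2.44) days to estimate sample size", and asks for 95 per group to detect a 1-day reduction with 80% power.

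**The concern.** MV duration depends partly on how a unit works, including when it judges a patient ready for a breathing trial. The Background section itself says that no specific parameters exist for deciding when to start. Some difference between ICUs in mean MV duration is therefore a reasonable expectation, although the protocol does not state one.

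If such a difference exists, it enters the plan in two places. The stated test pools all ICUs, so between-ICU variance stays in the error term. The planning SD comes from one hospital's ICU, so the sample size probably makes no allowance for that variance. The plan has almost no reserve above 80% power, so even a modest ICU effect takes it below its own target. ICU is known for every patient, so this loss is avoidable.

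**Working it through.** **Inputs from the protocol.** SD 2.44 days, difference 1 day, power 80% and 95 per group (5.2.6); two-sided alpha 0.05 (5.2.5). The ICC, the gap between ICUs and the number of ICUs are not given. They are assumptions below, shown as ranges.

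**Step 1: reproduce the plan's figure.**
- n per group = 2 × (1.960 + 0.842)² × 2.44² / 1² = 93.5, so 94 by the normal approximation. The t-based calculation gives 94.4, so 95. The stated figure reproduces.
- At 95 per group, SE = 2.44 × √(2/95) = 0.354. Power = Φ(1/0.354 − 1.960) = 0.806 (normal) or 0.802 (t-based).

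**Step 2: power if 2.44 is a within-ICU SD and ICU is ignored.** Pooled SD = 2.44 / √(1 − ICC).

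| Assumed ICC | Pooled SD | SE at 95 per group | Power, normal | Power, t-based | n per group for 80% (normal) |
|---|---|---|---|---|---|
| 0 | 2.44 | 0.354 | 0.806 | 0.802 | 94 |
| 0.02 | 2.465 | 0.358 | 0.799 | 0.794 | 96 |
| 0.05 | 2.503 | 0.363 | 0.786 | 0.782 | 99 |
| 0.10 | 2.572 | 0.373 | 0.764 | 0.760 | 104 |

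With ICU in the model, the residual SD returns to 2.44 and power to the first row.

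**Step 3: what those ICCs mean in days.** For two equal ICUs whose means differ by d days, pooled SD = √(2.44² + d²/4) and ICC = (d²/4) / (2.44² + d²/4).

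| d (days) | Implied ICC | Pooled SD | Power, normal |
|---|---|---|---|
| 0.5 | 0.01 | 2.453 | 0.802 |
| 1 | 0.04 | 2.491 | 0.790 |
| 2 | 0.14 | 2.637 | 0.743 |

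**Step 4: is there bias or type I error inflation?** The chance shift in the estimated effect has SD of about d × √(0.25 × 2/95) = 0.0725 × d. For d = 0.5, 1 and 2 days, 95% of shifts lie within ±0.07, ±0.14 and ±0.28 days, against a 1-day target. The shifts centre on zero.

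A simulation used 190 patients, 2 to 4 ICUs of equal expected size, two SAPS III strata, blocks of 10 and 2,000 runs per setting. Without ICU in the blocking, the unadjusted t test had a type I error of 0.045-0.057 and the mean estimate was unbiased.

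**Step 5: what blocking by ICU changes.** In the same simulation, the largest within-ICU difference between arms averaged about 6-8 patients (95th percentile 14-15) without ICU blocking and about 2-3 (95th percentile 4-5) with it. When allocation was blocked by ICU but the test stayed unadjusted, the type I error fell as low as 0.036 (three ICUs, ICC 0.10), which is somewhat conservative. The two changes therefore belong together.

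**The case against.** The best case against raising this is that nothing here is an error. Leaving ICU out of the blocking contradicts no other statement and does not invalidate the comparison. An ICU term in the analysis could sit in an SAP that is not shown. The text does not say that readiness protocols differ between ICUs, and the sample size and ethics sections name only one hospital, so a shared protocol is possible. If each ICU already holds its own envelopes, allocation is in effect blocked by ICU. Part of the methods text before section 5.2 is not available, so setting details there could not be checked.

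Most of this stands, and it sets the level of the point: a small improvement, not a defect. It does not remove the point. The blocking factor and the envelopes are fixed in this protocol, and 5.2.5 names a specific unadjusted test.

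A reader might be tempted to infer four stronger things:
- **That ICU differences confound the result.** They do not. Imbalance by ICU under randomisation is random, and step 4 shows no bias and no excess type I error.
- **That retesting and non-invasive ventilation also vary by ICU.** Section 5.2.4 sets common rules for both, as well as one trial duration. Readiness and tracheostomy practice are what remain open.
- **That very uneven splits are to be expected.** Blocks of 10 limit them. With one series across four equal ICUs, a split at least as uneven as 17:30 in some ICU occurs in about 13% of simulated trials.
- **That adjusting for ICU lifts power above plan.** That would require 2.44 to be an all-ICU SD. Section 5.2.6 takes it from one hospital's ICU, so adjustment restores the planned power and does not exceed it.

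**Conclusion.** The point holds as a modest loss of precision. More than one ICU recruits, ICU appears in neither the stated blocking nor the stated test, and the sample size rests on one hospital's ICU with almost no reserve. For an assumed ICC of 0.02 to 0.10, power falls from about 0.80-0.81 to between about 0.80 and 0.76, equivalent to needing 96 to 104 per group instead of 94-95.

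This rests on two assumptions that the protocol does not settle: that ICUs differ in mean MV duration, and that 2.44 is a within-ICU SD. If ICUs do not differ, nothing is lost. The estimate stays unbiased and the type I error holds in every case examined.

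**What to change.** 1. **Analysis.** Include ICU as a factor in the primary comparison of MV duration. If a rank test is used, use its stratified form (van Elteren) with ICU as the stratum. This costs one model term, needs no extra data, and remains available after enrolment has begun, provided it is set before outcomes by arm are seen.
2. **Allocation, only if enrolment has not begun.** State whether envelopes are held per ICU. If they are not, hold a separate blocked series at each ICU and use SAPS III as a covariate, or in at most two bands if the ICUs are few. The cost is re-preparing envelopes and accepting some incomplete blocks. Crossing too many factors makes this worse: six ICUs by two bands would give 12 strata of about 16 patients (190/12) against a block size of 10.
3. **Sample size text.** Say whether 2.44 days is a single-ICU SD, and that the 95 per group assumes ICU is accounted for in the analysis.

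### Randomisation is blocked by SAPS III but the protocol fixes only unadjusted tests, so part of the precision gained by stratifying is wasted if SAPS III predicts MV duration

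*Protocol*

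**What the plan says.** - **Allocation (protocol, 5.2.4):** "Randomization will be in blocks of 10, according to the SAPS III (simplified acute physiology score, version 3) score". No groups, cut-points or number of strata are given. I read the sentence as permuted blocks of 10 within SAPS III groups.
- **Continuous outcomes (5.2.5):** Student's "t test or Wilcoxon-Mann-Whitney test will be used for comparisons". This covers the primary outcome, since the abstract says "Primary outcome will be duration of mechanical ventilation".
- **Categorical outcomes (5.2.5):** "Categorical variables will be reported as percentages and compared by chi-square test or Fisher exact test, when appropriate".
- **Significance (5.2.5):** "Statistical significance level will be considered a two-tailed p-value lower than 0,05".
- **Sample size (5.2.6):** based on a mean and SD of "5.8 (± 2.44) days to estimate sample size", giving "95 patients in each group must be included to detect a 1-day reduction, considering a study power of 80"%.

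No stratified or SAPS III-adjusted analysis is mentioned.

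**The concern.** Blocking within groups of a prognostic score removes most of the chance imbalance on that score, which lowers the true variance of the treatment difference. A two-sample test that ignores the groups still estimates its standard error from the full outcome variance, including the part that the design has already controlled. The reported standard error is then larger than the real one, the confidence interval is wider than it needs to be, and the test rejects less often than 5% under the null.

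This is not just a matter of silence. The protocol names the tests, and the tests it names do not follow its own allocation scheme. What is at stake is efficiency and calibration for the primary outcome, in a trial sized with almost no margin above 80% power.

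**Working it through.** **Inputs from the protocol.** SD 2.44 days, difference 1 day, 95 per group and 80% power (5.2.6); two-sided 0.05 (5.2.5).

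**Assumed input.** R², the share of the variance of MV duration explained by the SAPS III groups. The protocol gives no figure, so a range from 0 to 0.20 is shown.

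**Step 1: reproduce the stated sample size.**
- Normal approximation: n = 2 × (1.960 + 0.842)² × 2.44² / 1² = 93.5, so 94 per group.
- Exact t-test calculation: 94.4, so 95 per group, as stated.
- At 95 per group, SE = 2.44 × √(2/95) = 0.354 and 1/0.354 = 2.825, so power = Φ(2.825 − 1.960) = 0.806.

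The stated figure is therefore right for an unadjusted t test with the unadjusted SD.

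**Step 2: effect of ignoring the groups.** With allocation balanced within groups, the true SE is 0.354 × √(1 − R²), while the unadjusted test goes on using 0.354. Hence:
- SE ratio, unadjusted to adjusted = 1/√(1 − R²)
- true size of the unadjusted 5% test = 2 × [1 − Φ(1.960/√(1 − R²))]
- unadjusted power = Φ((2.825 − 1.960)/√(1 − R²))
- adjusted power = Φ(2.825/√(1 − R²) − 1.960)
- n per group for 80% power when adjusted = 93.5 × (1 − R²), rounded up

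| Assumed R² | SE ratio | Size, unadjusted | Power, unadjusted | Power, adjusted | n per group, adjusted |
|---|---|---|---|---|---|
| 0 | 1.00 | 0.050 | 0.806 | 0.806 | 94 |
| 0.02 | 1.01 | 0.048 | 0.809 | 0.814 | 92 |
| 0.05 | 1.03 | 0.044 | 0.813 | 0.826 | 89 |
| 0.10 | 1.05 | 0.039 | 0.819 | 0.846 | 85 |
| 0.20 | 1.12 | 0.028 | 0.833 | 0.885 | 75 |

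**Step 3: check by simulation.** Blocks of 10 within two assumed strata, 190 patients, normal outcomes, 8,000 replicates per scenario.

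| Assumed R² | Size, t test | Size, adjusted | Power, t test | Power, adjusted |
|---|---|---|---|---|
| 0 | 0.044 | 0.044 | 0.798 | 0.798 |
| 0.10 | 0.040 | 0.051 | 0.823 | 0.852 |
| 0.20 | 0.032 | 0.055 | 0.825 | 0.877 |

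The Monte Carlo standard error of a size near 0.05 is √(0.05 × 0.95/8000) = 0.0024. At R² = 0 the t test is exact, so its 0.044 is noise. At R² = 0.20 the mean reported SE was 0.354 against a true 0.321, a ratio of 1.10. That is slightly below the formula's 1.12, which assumes perfect balance. Direction and rough size agree with step 2.

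**The case against.** The strongest reply is that nothing planned fails. The sample size uses the unadjusted SD and matches the t test, 80% power is met, and type I error is not inflated. That stands in full, and it makes this an efficiency point rather than a validity point.

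Second, the size rests wholly on an assumed R². The protocol does not say how far SAPS III predicts MV duration in COPD patients already ventilated for 48 hours. That also stands: at R² of 0.02 or less the excess in the standard error is 1% or less.

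Third, a statistical analysis plan that is not shown may add adjustment. It may, but the protocol itself fixes the tests for these comparisons, and they do not match its allocation.

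A reader might infer more than the protocol supports:
- **That the precision from stratifying is entirely lost.** It is not. The balance still helps the unadjusted test, whose power rises from 0.806 to 0.833 at R² = 0.20. Only the further gain to 0.885 is missed.
- **That the p-values are invalid.** The test errs only on the conservative side.
- **That ICU should be treated as a randomisation stratum.** Section 5.2.1 speaks of patients "admitted do the participant ICUs", so there may be several, but 5.2.4 does not name ICU as an allocation factor. The argument here does not reach it.
- **That power is lost by a known amount for mortality, extubation failure or tracheostomy.** Every figure above concerns a difference in means. No event rates are given from which a loss could be computed.

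**Conclusion.** The mismatch is in the text and should be corrected, but its consequence is modest. If the SAPS III groups explain 10% to 20% of the variance of MV duration, the unadjusted analysis reports a standard error about 5% to 12% too large and gives up about 3 to 5 percentage points of power (0.846 − 0.819 = 0.027; 0.885 − 0.833 = 0.052). If they explain 2% or less, the effect is negligible.

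These figures rest on three assumptions: that the sentence in 5.2.4 means stratified blocks, that the t test is used with the stated SD of 2.44 days, and that R² lies in the range shown. The size was not computed for the Wilcoxon-Mann-Whitney test.

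**What to change.** - **Section 5.2.4:** state the SAPS III groups used for blocking, with their cut-points.
- **Section 5.2.5, primary outcome:** make the SAPS III-adjusted comparison of MV duration primary. Use a linear model with treatment and SAPS III as covariate or, if a rank test is chosen, a van Elteren test by SAPS III group.
- **Section 5.2.5, binary outcomes:** use Mantel-Haenszel by SAPS III group.
- **Unadjusted tests:** keep the four named tests as sensitivity analyses.

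The cost is rewording in two sections. The van Elteren and Mantel-Haenszel analyses cannot be specified until the groups are written down; the linear model can use the score as a continuous covariate. SAPS III has to be recorded to randomise, so there is no extra data collection, and the sample size of 95 per group can stay as it is.
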